### Description of the Intervention

The interventions consist of (1) an audio-delivered intervention and (2) a written or printed intervention (such as posters or flyers) for education on leprosy, awareness-raising, and stigma reduction.

We will compare the effect of the interventions with a control group. The audio-delivered and written content will be developed based on local beliefs, misconceptions, and fears about leprosy identified in the baseline study. This will be done using participatory approaches. A group of persons affected by leprosy and a few members of the community will be formed, who will be guided by a researcher to develop the messages and materials (participatory development). The key messages of the audio-delivered and written interventions will be the same. The materials will be developed in the main languages spoken in the study areas: Nigerian Pidgin (Cross River State) and Hausa (Taraba State). The majority (>80%) of our target group speaks either Nigerian Pidgin or Hausa, which will hence be the language used for this study. The audio-delivered intervention will be incorporated into Audiopedia [42]. Audiopedia’s website was designed to provide access to open knowledge foremost on health, livelihood, and well-being to both community-based organizations and nongovernmental organizations and individuals. Community-based organizations and nongovernmental organizations can benefit from using Audiopedia as part of their social and behavior change communication strategy, as it enables them to search, download, embed, and share audio files. Approximately 5000 audio clips, with a total runtime of 150 hours, are available in 11 languages. Audiopedia was optimized for search engines, thus making contents easy to find. Audiopedia also provides several technological solutions to make audio-based contents accessible to both literate and illiterate audiences, such as solar-powered audio players, mobile web applications for smart (feature) phones, and Wi-Fi hotspots that can stream audio-based contents without the need for internet connectivity, etc.

### Participant Recruitment and Follow-Up

Persons affected by leprosy and community members will be selected based on purposive sampling. They will develop the content of the interventions. This is therefore, ideally, a diverse group of people who represent multiple perspectives. We will select participants based on purposive sampling to ensure adequate representation of age, gender, and villages.

The intervention will be implemented in North and South Nigeria, 2 areas that are very different. Therefore, we will cluster-randomize the interventions to ensure comparable groups are included in both areas. There are three different “groups” in each site (North and South): (1) the audio-delivered intervention, (2) the written materials intervention, and (3) no intervention (control group).

We will select 3 LGAs in North and South Nigeria (6 in total); each LGA will have either the audio-delivered or the written intervention or be a control group. The three LGAs per area will be selected based on their similarity in terms of literacy rate and endemicity of leprosy.

The interventions will be randomly allocated to clusters (LGAs) based on a random numbers list. This is a 2-stage random sampling. We will select a random sample of LGAs and a random sample of participants within each LGA. The participants in each LGA will be selected using the “spin the bottle” approach: a bottle will be spun in front of the most central place in the village (rural area) or neighborhood (urban area); the direction the bottle points at is the direction we start walking and counting. The first house to be included is selected by casting a die. Participant selection will be done by proportional sampling among the clusters. We will include the same participants at baseline and follow-up (a paired sample). This study protocol is reported in accordance with the SPIRIT statement (see checklist in Multimedia Appendix 1). The timeline schedule for participants during the study period is represented in Table 1, and a schematic description of the study flow chart is depicted in Figure 1.

**Table 1 table1:** Study schedule for enrollment, intervention, and assessment.

Schedule				Study period and time point										
				Enrollment		Allocation		Postallocation						Close out
				t_–1_		t_0_ (month 0)		t_1_ (baseline)		t_2_ (intervention)		t_3_ (6 months follow-up)		t_4_

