### Study Location and Setting

The study will be carried out in 6 local government areas (LGAs), 3 each in Cross River State (Boki, Calabar-South, and Obubra) and Taraba State (Jalingo, Yorro, and Zing). The 3 LGAs per area will be selected based on similarity in terms of literacy rate and prevalence of leprosy. Cross River is located in southern Nigeria, while Taraba is in the north. The total population of the study area is 940,540, estimated from the 2006 census, with 542,494 in Cross River and 398,046 in Taraba states. Both states have been selected because of the high prevalence of leprosy and G2D.

Cross River State notified a total of 106 new cases (17% with G2D) in 2019. The most common language spoken in Cross River State is Nigerian Pidgin. Over 90% of the people living in the selected LGAs in southern Nigeria speak Nigerian Pidgin. Other languages spoken in Cross River State include Efik, Ekoi, and Yala. The illiteracy rate (those with no schooling or primary or secondary education who cannot read at all) is 12.2% and 26.4% for male and female individuals, respectively. Occupations include farming, trading, and civil service employment. About 58% of women own mobile phones, compared with 71% among men [40]. Cross River State’s poverty index is 0.146, and the poverty headcount rate is 36.3%. The case notification rate for leprosy is 2.76 per 100,000 people based on 2020 data.

Taraba is among the 15 high-burden states for leprosy in Nigeria; an average of 100 new cases were detected between 2013 and 2017, with an average of 6% and 5% of children and G2D cases, respectively. This figure is likely to be underreported, considering the significant presence of isolated populations such as nomadic pastoralists and internally displaced people in the state.

The most common language spoken in the selected LGAs in Taraba State is Hausa; 80% to 90% of the people living in the selected LGAs in Northern Nigeria speak Hausa. Other languages spoken in Taraba State include Mummuye and Fulfulde. The illiteracy rate is 30.1% and 64.9% in Taraba State for male and female individuals, respectively. Occupations in Taraba include farming, mainly crop production and cattle rearing, petty trading, and civil service employment. The majority of men (71%) own a mobile phone, while only 44.6% of women do. Taraba State’s poverty index is 0.448, and the poverty headcount rate is 87.7%. The case notification rate for leprosy is 2.30 per 100,000 people.

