### Study Duration and Sample Size Calculation

This study’s duration will be 2 years. The sample size for the various components of the study is as follows. (1) A total of 200 community members (100 for each language per study area) will be included in the cross-cultural validation of the Explanatory Model Interview Catalogue Community Stigma Scale (EMIC-CSS) and Social Distance Scale (SDS), while 100 persons affected by leprosy (50 for each language per study area) will be included in the cross-cultural validation of the Internalized Stigma of Mental Illness (ISMI) scale and Rosenberg Self-Esteem Scale (RSES; see below). (2) A total of 770 community members will be included in the baseline and follow-up questionnaire interviews. This means a random sample of at least 385 persons in Taraba State (northern Nigeria) and at least 385 persons in Cross River State (southern Nigeria), which will consist of 114 in the audio intervention group, 114 in the written material intervention group, and 157 in the control group in each region.

This RCT will have three arms: (1) an audio-delivered intervention group, (2) a written material intervention group, and (3) a control group. The sample size calculation is based on 2 calculations. The intervention group calculation is based on an estimate of the difference in knowledge improvement between the audio-delivered intervention and the written material intervention groups. We used data from a perception study in India. In this study, postintervention scores improved by 12.5% after a poster intervention and community meetings. We estimate that the effect of posters alone would be an increase of 10%. We want to be able to detect an improvement of at least 15% between the audio-delivered and the written material intervention groups. The sample size of the intervention group is therefore based on a proportion 1 of 10 (estimated percentage of improvement in knowledge of leprosy in the written intervention group) and a proportion 2 of 25 (ie, an improvement of 15% or more). With a power of 80%, a significance level of .05, and a 15% loss to follow-up, 114 participants are needed in each intervention group.

We expect an increase of 2% in the knowledge score in the control group. The control group calculation is therefore as follows: proportion 1:10, proportion 2:2, power 80%, significance .05, and 15% loss to follow-up, resulting in 157 participants.

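### Proportional sampling among clusters, where clusters are LGAs, does not fit the fixed 114/114/157 per state; the rule needs reconciling and arm comparisons should account for state

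*Protocol article*

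**What the plan says.** Three sections of the protocol article bear on this.

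- **Study Duration and Sample Size Calculation.** "A total of 770 community members will be included in the baseline and follow-up questionnaire interviews", with a minimum of 385 in each state, made up of "114 in the audio intervention group, 114 in the written material intervention group, and 157 in the control group in each region".
- **Participant Recruitment and Follow-Up.** Three LGAs are taken in each state, and "each LGA will have either the audio-delivered or the written intervention or be a control group". The unit of allocation is explicit: "The interventions will be randomly allocated to clusters (LGAs) based on a random numbers list". After describing how households are found within a village or neighborhood, the section adds: "Participant selection will be done by proportional sampling among the clusters".
- **Study Location and Setting.** "The total population of the study area is 940,540, estimated from the 2006 census, with 542,494 in Cross River and 398,046 in Taraba states". No population is given for any single LGA. LGAs are chosen for similar literacy and leprosy burden; equal population is not a criterion.

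Data Management and Data Analysis lists Mann-Whitney, t, chi-square and z tests for the comparisons, a stepwise regression, and quantile regression to correct for demographic differences between arms if necessary. None of these is described as stratified by state. Results reports 811 baseline respondents, without a split by state, LGA or arm.

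**The concern.** With one LGA per arm per state, the numbers 114, 114 and 157 are quotas for individual LGAs. They come from power calculations and are the same in both states. A rule that samples LGAs in proportion to their size sets the numbers differently, and the article does not say which rule prevails.

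The fixed quotas do useful work. They make every arm half Cross River and half Taraba, so a difference between the states cancels in a crude comparison of arms. The recruitment section itself stresses how unlike the two areas are. Study Location and Setting gives female illiteracy of 26.4% in Cross River and 64.9% in Taraba, and poverty headcounts of 36.3% and 87.7%. If arm sizes followed LGA population instead, the state mix could differ between arms, and an unstratified test would carry part of the state difference into the arm comparison.

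**Working it through.** **1. The plan's own sizes.** Inputs from the sample size section: 10% v 25% for written v audio, 10% v 2% for the control calculation, 80% power, significance level .05, 15% loss. Sidedness is not stated; two-sided is assumed here. Formula: n = [p1(1−p1) + p2(1−p2)] × (1.960 + 0.842)² / (p1−p2)², then divided by 0.85.

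- 10% v 25%: (0.0900 + 0.1875) × 7.849 / 0.0225 = 96.8; 96.8/0.85 = 113.9. Stated: 114.
- 10% v 2%: (0.0900 + 0.0196) × 7.849 / 0.0064 = 134.4; 134.4/0.85 = 158.1. Stated: 157.
- 114 + 114 + 157 = 385 per state; 2 × 385 = 770.

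The quotas therefore come from the power calculation. Cluster size plays no part in them.

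**2. Reading A: proportional to population over all six LGAs, total fixed at 770.** Taraba's share is 398,046/940,540 = 42.3%.

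- Taraba: 770 × 0.4232 = 326, which is 59 below 385. Cross River: 444.
- Applied to 811, the same shares give 343 and 468.
- Keeping Taraba at 385 under this rule needs 385/0.4232, a total of about 910.

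**3. Reading B: proportional to population within each state, 385 per state.** Taraba keeps 385. The arms come out at 114/114/157 only if the three LGAs hold 114/385 = 29.6%, 29.6% and 157/385 = 40.8% of the population of the state's three study LGAs, and the largest is the one drawn for control. Even if both states had exactly those shares, independent random allocation would put the largest LGA in control in both states with probability 1/3 × 1/3 = 1/9.

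**4. Reading C: proportional over villages and neighborhoods inside an LGA.** The LGA quotas stand and there is no conflict.

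**5. Effect on an arm comparison.** Let s be the fraction of an arm's participants who come from Cross River, and D the outcome difference between states. The state contribution to a crude audio v written difference is (s_audio − s_written) × D. Under the fixed quotas both fractions are 114/228 = 0.5, so the contribution is zero. Under A or B, the two fractions are equal only if the ratio of the Cross River sample to the Taraba sample is the same in both arms. That depends on LGA populations and on the random draw, and the article supplies neither. D is not given either.

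**The case against.** The strongest reply is that the sentence on proportional sampling is loosely worded and the specific rule governs. The size measure and the level are unstated. The sentence follows directly on the account of selection by village or neighborhood, so Reading C may be what was meant. A team holding explicit quotas per arm and a minimum per state would hardly enroll 326 in Taraba on the strength of one undefined sentence. This stands in part: Reading C is plausible, but the same section uses the word clusters for LGAs, and the Limitations section shows no second meaning. The sentence needs correcting even if the practice was sound.

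A reader might infer that Taraba necessarily falls below its minimum. The article does not support that. The shortfall needs Reading A and a total held at 770, while the 385 is a floor, so a larger total could satisfy both rules.

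A reader might also infer a definite bias of some number of points between audio and written. That cannot be sustained. It would need LGA population shares and a state difference in outcome, neither of which is given; similar arm shares in the two states would make the bias close to zero. The illiteracy and poverty figures show that the states differ, but they are not outcome differences.

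Loss of power is not shown either. Each calculated size is applied in both states, giving arm totals of 228, 228 and 314, so moderate departures from the quotas would leave the arms above the sizes calculated.

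Finally, state may enter the analysis through a fuller plan that is not at hand, and applying the full sample size in each state is compatible with comparing arms within state. That is fair, and it is why the request is to make this explicit.

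**Conclusion.** The point holds as an unreconciled sampling rule. With clusters defined as LGAs, sampling proportionally among them does not fit fixed numbers per LGA. The consequence depends on the reading: about 326 in Taraba against 385 if proportional to population over all six LGAs at 770; 385 kept but arm sizes driven by LGA population if proportional within state; no conflict if proportional only within an LGA. Under the first two readings, an equal state mix across arms is not assured, and the document's figures cannot size the imbalance. The 811 enrolled exceed the planned 770 by 41 with no breakdown, so a reader cannot tell which rule was followed. This is a minor point. Baseline recruitment is complete and rewording cannot change who was sampled, but the analysis had not begun at the time of submission and can still be protected.

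**What to change.** 1. Replace the sentence with one that says the number per LGA is fixed by arm (114/114/157 in each state), and that within an LGA this number is spread over villages and neighborhoods in proportion to population. If a different rule was used in the field, state that rule instead.
2. Report the 811 enrolled by LGA and arm.
3. Stratify or adjust every between-arm comparison by state. Arms are allocated within state, so this follows the design, and it removes confounding of arm with state whichever sampling rule was applied.

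The cost is one sentence, one table of counts that the investigators should already hold, and a state term or stratum in the analysis. No new data are needed.

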**Enrollment**														
	Eligibility screening		✓											
	Informed consent		✓											
	Randomization and allocation				✓									
**Intervention group**														
	Audio-delivered intervention								✓					
	Written								✓					
	Control (no intervention)													
**Assessments**														
	**Baseline variables**													
		KAP^a^, EMIC-CSS^b^, and SDS^c^					✓							
		RSES^d^ and L-ISMI^e^ scale					✓							
		CNA^f^					✓							
	**Outcome variables**													
		KAP, EMIC-CSS, and SDS									✓			
		RSES and L-ISMI scale									✓			
**Analysis**														
	Data analysis												✓	

^a^KAP: knowledge, attitudes, and practices.

^b^EMIC-CSS: Explanatory Model Interview Catalogue Community Stigma Scale.

^c^SDS: Social Distance Scale.

^d^RSES: Rosenberg Self-Esteem Scale.

^e^L-ISMI: Leprosy-adapted Internalized Stigma of Mental Illness.

^F^CNA: Communication Needs Assessment.

**Figure 1 figure1:**
[figure not shown]
Study flow chart. LGA: local government area.

### Primary and Secondary End Points

The outputs of this study will be an audio-delivered intervention and written or printed health education material for education on leprosy, awareness-raising, and stigma reduction.

In addition, all 4 scales will be translated and cross-culturally validated in Nigerian Pidgin and Hausa languages as part of this study. The qualitative outcomes are knowledge and attitudes toward (persons affected by) leprosy (eg, local beliefs, fears, and misconceptions).

Outcome measures used to be assessed at baseline and follow-up are as follows:

Demographic information: to disaggregate data by gender, the “knowledge, attitudes, and practices” (KAP) measure includes a form to collect demographic information.The KAP measure, as used in a study in India [16], covers 8 main topics: early symptoms, cause, mode of transmission, treatment, prevention, curability, contagiousness when on treatment, and prevention of disabilities. The KAP is a questionnaire and has not been formally validated as a scale (nor will it be used as a scale). We will translate and pilot test the KAP measure.Community stigma, using the EMIC-CSS (used in Nigeria but not validated in Nigerian Pidgin and Hausa yet [17]).Desired social distance toward persons affected by leprosy as a proxy for attitudes and fear, using the SDS (used among persons affected by leprosy in Nigeria but not validated in Nigerian Pidgin and Hausa yet [17]).Self-esteem and internalized stigma of persons affected by leprosy, using the RSES (used in Nigeria but not validated in Nigerian Pidgin and Hausa yet) and the leprosy-adapted ISMI (used among persons affected by leprosy and used in Nigeria but not formally validated yet [17]).

### Data Collection

#### Overview

We will use a mixed methods approach and collect qualitative data (in-depth interviews and focus group discussions [FGDs]) and quantitative data (the KAP measure, EMIC-CSS, SDS, communication needs assessment, RSES, and ISMI). We will also collect demographic information (including literacy levels) from each participant.

This study consists of the steps and phases outlined in the following subsections.

#### Step 1

None of the tools listed in step 2 have been validated in Nigerian Pidgin and Hausa yet; therefore, they will be cross-culturally validated before use. We will assess conceptual, item, semantic, operational, and measurement equivalence using a framework for cross-cultural equivalence testing based on the work of Herdman et al [43], Terwee et al [44], and Stevelink and van Brakel [45]. In addition, the interview and group discussion guides (outlined in step 2) will be pilot tested among a small sample of participants before use. The KAP measure will be translated and pilot-tested.

#### Step 2

A baseline study to assess the perceptions of community members using mixed methods will be conducted, consisting of both in-depth interviews and FGD sessions and questionnaires (KAP, EMIC-CSS, and SDS). A communication needs assessment will be conducted as part of the baseline study to determine the most appropriate mode of delivery of the audio intervention and the most appropriate duration and frequency of the audio intervention. We will also conduct a baseline study among the persons affected by leprosy group who will be involved in the development of the interventions. Self-esteem and internalized stigma will be assessed using in-depth interviews, RSES, and ISMI.

#### Step 3

The participatory development of the audio-delivered and written content of the interventions is based on the knowledge gaps, beliefs, misconceptions, fears, and community attitudes identified in the baseline study. We will use the “6 steps in quality intervention development (6SQuID) framework [46], consisting of (1) defining and understanding the problem and its causes, (2) identifying which causal or contextual factors are modifiable: which have the greatest scope for change and who would benefit most, (3) deciding on the mechanisms of change, (4) clarifying how these will be delivered, (5) testing and adapting the intervention, and (6) collecting sufficient evidence of effectiveness to proceed to a rigorous evaluation. The final step of 6SQuID (step 6) is part of step 5 of this study—evaluation. The group of persons affected by leprosy who play a leading role in the development of the messages and materials (participatory development) will codetermine both the content of the materials (based on the knowledge gaps, beliefs, misconceptions, fears, and community attitudes identified in the baseline study) and the mode of delivery (based on the most appropriate means of communication determined by the communication needs assessment conducted as part of the baseline study).

#### Step 4

Implementation of the interventions in the study areas will be done in 2 groups: one intervention group will receive the audio-delivered intervention, and the other intervention group will receive the written intervention (poster or flyer). A control group will not receive any intervention. The groups will be cluster-randomized.

#### Step 5

Step 5 involves evaluating the impact of (1) the intervention on the community and (2) developing the intervention on persons affected, using the same mixed methods as the baseline studies (described in step 2). It should be noted that the in-depth interviews at baseline are mainly conducted to get insight into specific fears, local beliefs, and misconceptions about leprosy among community members, as well as insight into the self-esteem and internalized stigma of persons affected by leprosy. At follow-up, the communication needs questionnaire will not be administered anymore. In addition, FGDs will be held with community members at baseline and follow-up in the 6 LGAs and with the persons affected by leprosy group. In addition to further exploring themes that arose during the in-depth interviews, additional questions will be asked (at follow-up) to get insight into, among other things, awareness of, experiences with, and exposure or access to the audio and written interventions; thoughts about content; mode of delivery and frequency; and strengths and points of improvement.

